## Annex 3. Subject Diary Card

### Notes for completing this card:

- 1) Every day, complete the diary card within 2 weeks after DNA vaccination and 4 weeks after rTV vaccination, and record any discomforts occurring at other times on the diary card.
- 2) Please record the non-prescription drugs or other treatments to alleviate local reactions;
- 3) If you have any symptoms that cannot go away by themselves, please contact the study staff;
- 4) After you have completed the diary card on the day, please give the completed diary to the study staff at your next visit.
- 5) For safety, after rTV vaccination, subjects themselves may not remove the gauze covering the vaccination site without special circumstances

## Diary Card

Screening number    □□□□□□

Subject initials    □□□□

Recording date 20    Year    Month    Day

Day after vaccination (day 1-28)

Axillary temperature:

A.M. (6:00- 8:00)      °C

P.M. (8:00- 10:00)      °C

Have you participated in sports or heavy physical labor?    Yes    No

Type of sports or heavy physical labor:

Duration:          hours

Please record the physical discomfort after vaccination:

| Name of symptom | Duration of symptom | Time to relieve |
|-----------------|---------------------|-----------------|
|                 |                     |                 |

Please record the medications after vaccination:

| Drug name | Reason for medication | Time starting medication | Dosage of medication | Route of administration                                         | Time of ending medication |
|-----------|-----------------------|--------------------------|----------------------|-----------------------------------------------------------------|---------------------------|
|           |                       |                          |                      | 1. Oral; 2. intramuscular injection; 3. Intravenous; 4. Topical |                           |

|  |  |  |  |                                                                             |  |
|--|--|--|--|-----------------------------------------------------------------------------|--|
|  |  |  |  | 1. Oral; 2.
intramuscular
injection; 3.
Intravenous; 4.
Topical |  |
|--|--|--|--|-----------------------------------------------------------------------------|--|

Subject's signature:

Date:    □□□□Year□□Month□□Day

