Based on the data obtained from the Phase Ia clinical trial, which showed that the rTV vaccine was well tolerated at both 1 and 2 doses, with 2 doses being the highest safe dose determined in this phase, the Phase Ib clinical trial will use 2 doses as the vaccination dose for the rTV vaccine.

After immunization, participants will be observed for 24 hours, during which researchers will closely monitor local and systemic adverse reactions and complete raw data and CRF forms. Participants will then be given daily report cards and instructed on how to complete them. Participants must fill out the daily report cards every day for 2 weeks after DNA vaccination and for 4 weeks after rTV vaccination, and record any abnormalities that occur between follow-up visits on the daily report cards, which will be submitted to researchers at the next follow-up visit (Appendix 3). During the 2 weeks after DNA vaccination and the 4 weeks after rTV vaccination, participants must also complete a temperature chart for the respective periods. All adverse events occurring between follow-up visits will be recorded in the raw data forms, transcribed to the CRF forms, and entered into the database. Follow-up visits to the hospital will occur at weeks 1, 2, and 4 after DNA vaccination, and on days 3, weeks 1, 2, 4, 8, 12, 16, 20, and 24 after rTV vaccination. At each follow-up visit, researchers will record all participant-related data, including physical examinations and laboratory tests, in the raw

data forms and transcribe them to the CRF forms. During the trial, Phase Ib participants will need to visit Peking Union Medical College Hospital at least 20 times for trial-required visits, 14 of which will involve venous blood sampling. The immunization schedule, trial plan, and venous blood sampling plan for the Phase Ib trial are detailed in Tables 5, 6, and 7, respectively.

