|                   | Injection Site
Erythema                         | Diameter <1.5 cm                                                                  | Diameter 1.5–3 cm                                                                                                     | Diameter >3 cm                                                 | Gangrene or exfoliative dermatitis |
|-------------------|----------------------------------------------------|-----------------------------------------------------------------------------------|-----------------------------------------------------------------------------------------------------------------------|----------------------------------------------------------------|------------------------------------|
| Systemic Symptoms |                                                    |                                                                                   |                                                                                                                       |                                                                |                                    |
| Headache          | Does not affect activity, no treatment required    | Transient, affects daily activities, requires treatment (non-narcotic analgesics) | Severely affects daily activities, occasional narcotic treatment required                                             | Persistent, requires repeated narcotic treatment               |                                    |
| Chills            | Occasional OTC non-steroidal antipyretics required | Limits daily activities >6 hours, or requires repeated non-steroidal antipyretics | Severely affects daily activities, requires prescription medication                                                   | Hospitalization required                                       |                                    |
| Fatigue           | Reduced normal activity <48 hours                  | Reduced normal activity 20%–50% >48 hours                                         | Severely affects daily activities, reduces normal activity >50%, unable to work                                       | Unable to care for self, emergency or hospitalization          |                                    |

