| Myalgia           | Does not affect daily activities                   | Tenderness in non-injection site muscles, slightly limits daily activities        | Severe muscle tenderness, severely affects daily activities                                                           | Severe symptoms, muscle necrosis, emergency or hospitalization |                                    |
| Arthralgia        | Mild pain, does not limit daily activities         | Moderate pain, slightly limits daily activities                                   | Severe pain, severely affects daily activities                                                                        | Hospitalization required                                       |                                    |
| Nausea            | Mild or transient, does not affect normal eating   | Affects normal eating                                                             | Unable to eat, requires outpatient IV fluids                                                                          | Hospitalization required                                       |                                    |
| Vomiting          | 1 episode in 24 hours                              | 2–5 episodes in 24 hours                                                          | >6 episodes in 24 hours or IV fluids required                                                                         | Requires hospitalization or alternative nutrition              |                                    |
| Diarrhea          | Mild or transient, 2–3 episodes/day, lasts <1 week | Moderate or persistent, 4–5 episodes/day, or diarrhea >1 week                     | >6 episodes/day, or bloody stools, orthostatic hypotension, electrolyte imbalance, requires >2L IV fluids in 24 hours | Hypotensive shock, requires hospitalization                    |                                    |
| Cough             | Transient, no treatment required                   | Paroxysmal cough, treatment effective                                             | Persistent cough, treatment ineffective                                                                               | Emergency or hospitalization                                   |                                    |

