**Report form of treatment of systemic and local reactions (including non-prescription drugs)**

| NO.                                                            | Drug name | Dosage | Times per day | Duration of use (from Month Day to Month Day) | Reason for using the drug and the effect |
|-----------------------------------------------------------------------|------------------|---------------|----------------------|------------------------------------------------------|-------------------------------------------------|
| 1                                                                     |                  |               |                      |                                                      |                                                 |
| 2                                                                     |                  |               |                      |                                                      |                                                 |
| 3                                                                     |                  |               |                      |                                                      |                                                 |
| 4                                                                     |                  |               |                      |                                                      |                                                 |
| 5                                                                     |                  |               |                      |                                                      |                                                 |
| If other treatments are used, please explain them specifically |                  |               |                      |                                                      |                                                 |
|                                                                       |                  |               |                      |                                                      |                                                 |

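### The diary's symptom table has no field for activity limitation, eating or episode count, so Grade 2 versus 3 for most systemic symptoms rests largely on questioning at the next visit

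*Protocol*

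**What the plan says.** Annex 3 of the protocol prints the diary. Under the prompt "Please record the physical discomfort after vaccination" stands a blank table with the columns "Name of symptom | Duration of symptom | Time to relieve". No symptoms are preprinted. The same card takes axillary temperature twice a day and, under "Please record the medications after vaccination", drug name, reason, start, dosage, route (including intravenous) and end. A separate treatment form has a column headed "Reason for using the drug and the effect". The only activity question is "Have you participated in sports or heavy physical labor", which asks about exertion, not about limitation.

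Annex 2 grades systemic symptoms on other information. Grade 2 fatigue is "Reduced normal activity 20%–50% >48 hours"; Grade 3 vomiting is ">6 episodes in 24 hours or IV fluids required".

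Section 6.5.4 has participants enter other adverse events on the card and has those events graded by Annex 2. Section 6.4.2 sets the contacts: "Follow-up visits to the hospital will occur at weeks 1, 2, and 4 after DNA vaccination", and after rTV at day 3, weeks 1, 2 and 4, and later. Section 6.5 adds 24 hours of direct observation after each immunization and lets the CRF prevail over the card where they differ.

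Grade 3 or higher systemic reactions are a primary safety endpoint (section 6.2.1.1). Related events of Grade 3 or higher drive the halting rule (sections 6.4.2 and 6.7.2) and end vaccination for the individual (sections 6.5.8 and 6.7.1).

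**The concern.** The diary is the only record made on the day the symptom occurs, once the 24-hour observation has ended. If it omits the quantity on which the grading scale turns, the grade has to be reconstructed at a visit. The step most exposed is Grade 2 to Grade 3, and that step decides whether a primary event has occurred and whether it counts towards halting.

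The groups are small (12, 12, 6 and 6), and the halting threshold lies between two and three events. One event graded a step differently could therefore matter.

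**Working it through.** The protocol gives no figure to reproduce. The check sets Annex 2 beside the card and then bounds the wait to the next visit.

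**Step 1. What separates Grade 2 from Grade 3, and what the card offers.**

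| Systemic row in Annex 2 | Basis of the Grade 2/3 line | Help from the card |
|---|---|---|
| Headache | Degree of activity loss; class of analgesic | Partial: drug name |
| Chills | Degree of activity loss; prescription drug | Partial: drug name |
| Fatigue | Share of activity lost; ability to work | None |
| Myalgia | Degree of activity loss; tenderness | None |
| Arthralgia | Degree of activity loss; pain | None |
| Nausea | Effect on eating; intravenous fluids | Partial: route |
| Vomiting | Episodes in 24 hours; intravenous fluids | Partial: route |
| Diarrhoea | Episodes per day; clinical signs; intravenous volume | Partial: route and dosage |
| Other discomfort | Degree of activity loss; need for medication | Partial: any drug entry |
| Cough | Response to treatment | Effect column of the treatment form |
| Allergic reaction | Clinical signs | Examination at the visit |
| Lymphadenopathy | Regions, node size, or tenderness with activity loss | Mostly examination at the visit |

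Rows that turn on activity, eating or episode count: the first nine, so 9 of 12. Rows with a card field for that quantity: 0 of 9. Rows partly informed by medication entries: 6. Rows with no help: 9 − 6 = 3 (fatigue, myalgia, arthralgia).

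The count involves some judgement. Leaving nausea out gives 8; adding lymphadenopathy, which has activity as one of its alternatives, gives 10. It is a majority on any of these counts.

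The duration column does little at this line. The time limits for fatigue (48 hours), chills (6 hours) and diarrhoea (1 week) help to define Grade 2, but none of the three Grade 3 entries has such a limit.

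**Step 2. Longest wait to the next visit (difference between successive visit days).**

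- After DNA (days 7, 14, 28): 7 − 0 = 7, 14 − 7 = 7, 28 − 14 = 14 days.
- After rTV (days 3, 7, 14, 28): 3 − 0 = 3, 7 − 3 = 4, 14 − 7 = 7, 28 − 14 = 14 days.
- The first day is observed, so the first interval leaves at most 7 − 1 = 6 days after DNA and 3 − 1 = 2 days after rTV.

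Daily completion runs for 2 weeks after DNA and 4 weeks after rTV. The 14-day gap therefore falls within the daily-diary period only after rTV. The low-dose halting assessment covers the two weeks after each DNA dose, where the longest gap is 7 days.

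**Step 3. How sensitive the results are to one grade.** Moving one participant across the line changes a group's proportion by 1/12 = 8.3 percentage points or 1/6 = 16.7 points. This shows leverage only; it does not estimate how often misgrading would occur.

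**The case against.** The strongest reply is that the diary is an aide-memoire and not the grading instrument. Events go to the raw data form and CRF, the CRF prevails, and the head of the clinical trial unit reviews the grading (section 6.5.6). Those forms and the SOPs are not shown and may already hold activity and episode fields. Recall is also helped by dated same-day entries, and Annex 3 tells participants to contact staff about symptoms that do not go away by themselves. Several Grade 3 markers, such as narcotic use, intravenous fluids or inability to work, are hard to forget.

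Much of this stands, and it limits the point. It does not remove it: a CRF completed at visits still depends on what the participant remembers, and for fatigue, myalgia and arthralgia the card gives no prompt at all.

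A reader might infer more than the protocol supports:

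- That the diary records nothing but name, duration and relief. This is true of the symptom table only. Fever can be graded from the temperature entries, and medication is recorded with its route.
- That grades are always rebuilt one to two weeks later. Two weeks is the upper bound, and it applies only in weeks 2 to 4.
- That misgrading will differ by arm because of unblinding. Under section 6.10.4, participants and clinical observers lose blinding 3 days after rTV, so this does not touch the DNA doses. A new card would not cure it either.
- That the symptom rates in Annex 6 (fatigue 50%, headache 40%, myalgia 20%, nausea 20%) size the problem. They are rates after smallpox vaccination, not split by grade, and they say nothing about how many events lie near the Grade 2/3 line.

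**Conclusion.** The point holds as a weakness in how a primary endpoint is measured. The diary's symptom table lacks the grading quantity for 9 of 12 systemic symptoms. Medication entries help in part for six and not at all for three. Grade 2 versus 3 then rests largely on questioning up to 7 days later in weeks 0 to 2 (3 to 4 days in week 1 after rTV) and up to 14 days later in weeks 2 to 4.

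This assumes that no other same-day record exists after the 24-hour observation; the protocol shows none. It does not assume that the CRF lacks these fields.

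The protocol does not support the claim that Grade 3 counts will be wrong, or by how much. The effect cannot be quantified from it, and the synopsis reports no vaccine-related event of Grade 3 or higher among the 12 Phase Ia subjects, who received rTV alone. The change is worth making because it is cheap.

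**What to change.** Reprint the Annex 3 card with the Annex 2 systemic symptoms listed, each answered yes or no every day. For each yes, add one same-day field that mirrors the Annex 2 criterion:

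- effect on daily activities, with an approximate percentage reduction for fatigue;
- effect on eating, for nausea;
- episodes in 24 hours, for vomiting and diarrhoea.

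Keep the temperature entries, the medication table and the free-text lines. Check that the raw data form and CRF carry matching fields, and add them where they do not.

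The cost is a new diary page, possibly some CRF fields, and a minute or two more per day for participants. More mild symptoms will be recorded. The change alters no dose, schedule or stopping rule, and it does not remove the effect of unblinding after rTV.

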**Report form of treatment of systemic and local reactions (including non-prescription drugs)**

| NO.                                                            | Drug name | Dosage | Times per day | Duration of use (from Month Day to Month Day) | Reason for using the drug and the effect |
|-----------------------------------------------------------------------|------------------|---------------|----------------------|------------------------------------------------------|-------------------------------------------------|
| 1                                                                     |                  |               |                      |                                                      |                                                 |
| 2                                                                     |                  |               |                      |                                                      |                                                 |
| 3                                                                     |                  |               |                      |                                                      |                                                 |
| 4                                                                     |                  |               |                      |                                                      |                                                 |
| 5                                                                     |                  |               |                      |                                                      |                                                 |
| If other treatments are used, please explain them specifically |                  |               |                      |                                                      |                                                 |
|                                                                       |                  |               |                      |                                                      |                                                 |

## Annex 4. Summary of Test Results for HIV-1 DNA Vaccine

| Test Item                                               | Test Method                            | Quality Standard                                                                                                         | pGP140
(20041123) | PGPNEF
(20041124) |
|---------------------------------------------------------|----------------------------------------|--------------------------------------------------------------------------------------------------------------------------|----------------------|----------------------|
| Appearance                                              | Visual inspection                      | Clear, colorless liquid, free of foreign matter                                                                          | Pass                 | Pass                 |
| pH Value                                                | Chinese Pharmacopoeia                  | 6.7–7.7                                                                                                                  | Pass                 | Pass                 |
| Fill Volume                                             | Chinese Pharmacopoeia                  | Average fill volume not less than the labeled volume
(1.0 ml/vial), each vial not less than 93% of the labeled volume | Pass                 | Pass                 |
| Sterility Test                                          | Chinese Pharmacopoeia                  | No microbial growth                                                                                                      | Pass                 | Pass                 |
| Identification Test
(Restriction Enzyme Mapping)     | Restriction enzyme mapping             | Consistent with expected results                                                                                         | Pass                 | Pass                 |
| Residual E. coli Genomic DNA                            | Solid-phase slot blot hybridization    | $\leq 2$ µg/mg plasmid                                                                                                   | Pass                 | Pass                 |
| Residual Host Cell Protein                              | Chinese Biological Products Regulation | $\leq 1$ µg/mg plasmid                                                                                                   | Pass                 | Pass                 |
| Endotoxin Content                                       | Chinese Pharmacopoeia                  | $\leq 5$ EU/mg plasmid                                                                                                   | Pass                 | Pass                 |
| Residual RNA (Agarose Gel Electrophoresis)              | Agarose gel electrophoresis            | No other bands or diffuse nucleic acid bands except plasmid band                                                         | Pass                 | Pass                 |
| Purity Test (UV Absorption)                             | UV absorption                          | $A_{260}/A_{280} \geq 1.75$                                                                                              | Pass                 | Pass                 |
| Concentration Test (UV Absorption)                      | UV absorption                          | 1.8–2.2 mg/ml                                                                                                            | Pass                 | Pass                 |
| Plasmid Conformation Test (Agarose Gel Electrophoresis) | Agarose gel electrophoresis            | Circular plasmid $\geq 90\%$                                                                                             | Pass                 | Pass                 |
| Residual LiCl                                           | ICP-MS                                 | $\leq 1$ µg/mg plasmid                                                                                                   | Pass                 | Pass                 |
| In Vitro Gene Expression Test (Western Blot)            | Western Blot                           | pGP140: Specific band at 130 kDa; pGPNEF: Specific band at 160 kDa                                                       | Pass                 | Pass                 |
| Abnormal Toxicity Test                                  | Chinese Biological Products Regulation | Guinea pig test: Guinea pigs survive and gain weight;
Mouse test: Mice survive and gain weight                        | Pass                 | Pass                 |

|                                               |            |                                                                                        |      |      |
|-----------------------------------------------|------------|----------------------------------------------------------------------------------------|------|------|
| Humoral Immunogenicity Test (ELISA)    | ED50 ELISA | $ED50 \leq 100 \mu\text{g}$ (pGP140); $ED50 \leq 80 \mu\text{g}$ (pGPNEF)              | Pass | Pass |
| Cellular Immunogenicity Test (ELISPOT) | ELISPOT    | Positive cellular immune response rate in mice vaccinated with DNA vaccine $\geq 60\%$ | Pass | Pass |

